### Inclusion Criteria

Participants will be eligible if they are male patients, aged 30-60 years, have newly diagnosed OSA with an AHI ≥15 episodes per hour, are indicated to CPAP therapy, and are interested in our adjunct tele-RHB program.

### Exclusion Criteria

Participants are excluded if they have another type of OSA treatment, chronic corticosteroid therapy or long-term oxygen therapy; they are also excluded if they have at least one of the following health problems: central sleep apnea, chronic obstructive pulmonary disease III or IV, severe pulmonary hypertension, New York Heart Association III or IV, acute coronary syndrome, heart failure, ejection fraction <40%, electrocardiographic-documented heart arrhythmia, severe heart valve disease, cerebrovascular disease, psychiatric disease, and physical disability; in addition, they will be excluded if they do not cooperate during the intervention or do not follow the tele-RHB program and CPAP therapy protocol.

### Recruitment, Enrollment, and Procedure

The patients who meet the inclusion criteria will be recruited from the Sleep Centre of the FNUSA-ICRC. The details of the study overview are shown in Table 1. On the first visit, patients will undergo polysomnography (PSG), blood sampling for lipid profile, and completion of the Epworth Sleepiness Scale (ESS) with a known score. Those who are found to have moderate to severe OSA will be contacted for further intervention alongside the standard CPAP therapy. These patients will be verbally informed and will receive an information leaflet about the ongoing study of the 12-week tele-RHB program. Then, they will complete anthropometric and spirometric examinations, measurements of maximal inspiratory mouth pressure (MIP) and maximal expiratory mouth pressure (MEP) as well as body composition, 6-minute walk test (6MWT), and QoL questionnaires in the Cardiovascular Rehabilitation Clinic at the University Hospital Brno (CRC-UHB). After that, during the interview with a physiotherapist, participants will receive detailed and comprehensive information regarding their possible participation in the study. Then, potential participants will be given at least 24 hours to decide before signing the informed consent.

On the second visit, patients who agreed to participate in the study will sign the informed consent form and will be then randomized 1:1 to the intervention or control group.

On the third visit, participants of both groups will undergo individual titration of CPAP therapy at the Sleep Centre of the FNUSA-ICRC. The intervention group will subsequently receive education about the tele-RHB program, along with theoretical and practical instruction on its individual components in the CRC-UHB. Participants of the intervention group will also receive a training brochure containing information needed for the tele-RHB program with remote supervision by a physiotherapist.

After the completion of the 12-week tele-RHB program, on the fourth visit, participants of both groups will undergo the same examinations and measurements as those conducted at the baseline, at the Sleep Centre of the FNUSA-ICRC and in the CRC-UHB.

After 1 year from the 12-week tele-RHB program’s completion, on the fifth visit, participants of both groups will undergo the same examinations and measurements as they did at the baseline in both health facilities.

**Table 1 table1:** An overview of the study flow.

Timeline	Preintervention outcome examination (0-7 days)			Treatment settings (8-28 days)		Intervention (12 weeks)		Postintervention outcome examination (1-5 days after)		Follow-up (1 year after)
	First visit	Second visit	Third visit		N/A^a^		Fourth visit		Fifth visit	
Screening	✓									
Signed informed consent form		✓								
Interview	✓									
Randomization		✓								
Polysomnography	✓						✓		✓	
Epworth Sleepiness Scale	✓						✓		✓	
Lipid profile	✓						✓		✓	
Anthropometry	✓						✓		✓	
Spirometry	✓						✓		✓	
Maximal mouth pressures	✓						✓		✓	
6-minute walk test	✓						✓		✓	
Body composition	✓						✓		✓	
Questionnaires	✓						✓		✓	
CPAP^b^ titration			✓							
Education			✓							
Teleconsultations					✓					

^a^N/A: not applicable.

^b^CPAP: continuous positive airway pressure.

### Randomization

Participants will be randomized 1:1 to the intervention and control group by a noninvestigating member of the research group in the CRC-UHB with the help of the website “randomization.com” [22] into 6 blocks of 8 and 1 block of 2 participants. Participants and caregivers will be instructed not to comment on their ongoing therapy. The outcome assessor will be blinded. Physiotherapists who educate the intervention group participants about the tele-RHB program and who carry out regular teleconsultations during this program are the only unblinded members of the research group.

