## Methods

### Study Design

This study is a 2-arm parallel single-blind randomized controlled trial (registered on ClinicalTrials.gov: NCT04759456), with the per-protocol analysis investigating the effect of the tele-RHB program among 50 male patients with newly diagnosed OSA indicated to CPAP therapy. Patients were recruited from the Sleep Centre of the International Clinical Research Center of St Anne's University Hospital in Brno (FNUSA-ICRC). After providing informed consent, the patients will be randomized to the 12-week tele-RHB program along with CPAP therapy; 25 patients will be randomized to the intervention arm, and 25 will be in the control arm (CPAP therapy alone) in a 1:1 ratio, following the methods described below (Figure 1).

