## Results

Study recruitment began on October 25, 2021, and the estimated study completion date is December 2024. Analyses will be performed to examine whether the combination of the tele-RHB program and CPAP therapy will be more effective in the reduction of OSA severity and improvement of QoL, body composition and circumferences, exercise tolerance, lipid profile, as well as respiratory muscle and lung function, compared to CPAP therapy alone.

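### Fixed block sizes (six of 8, one of 2) in a single unstratified stream leave some allocations deducible if the physiotherapist who interviews before consent knows the sizes and earlier assignments

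*Protocol article*

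**What the plan says.** The Randomization section of the protocol article assigns men 1:1 "into 6 blocks of 8 and 1 block of 2 participants", using a website. The assignment is made "by a noninvestigating member of the research group in the CRC-UHB". The same section says that the physiotherapists who teach tele-RHB and hold the teleconsultations "are the only unblinded members of the research group".

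Under Recruitment, Enrollment, and Procedure, patients "will be recruited from the Sleep Centre of the FNUSA-ICRC"; no strata are mentioned. After polysomnography, the sleepiness scale and the baseline tests at the rehabilitation clinic, "during the interview with a physiotherapist, participants will receive detailed and comprehensive information regarding their possible participation in the study". They then have at least 24 hours to decide. At the second visit those who agree "will sign the informed consent form and will be then randomized 1:1 to the intervention or control group". CPAP titration and tele-RHB education follow at the third visit.

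The article does not say whether the interviewing physiotherapist is one of the treating ones, who apart from the list holder knows the block sizes, or in what order the blocks are used.

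**The concern.** With constant block sizes, anyone who knows the size and has followed the sequence can tell when one arm is used up within a block. The rest of that block is then certain. Keeping the list with a non-investigator protects the list itself, but does not prevent this deduction.

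It matters here because the step before consent is a conversation with a member of the profession that delivers the intervention, apparently at the same clinic. Interest in the program is an eligibility criterion, disease severity may already be known by then, and the man has time to decide. A recruiter who knows the next assignment could, without intending to, encourage or discourage particular men. Several primary outcomes are self-reported (sleepiness, SF-36) or depend on effort (walk distance, mouth pressures), so differences in motivation between the arms could affect them.

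**Working it through.** **Inputs.** Block scheme: six of 8 and one of 2 (Randomization). Arms: "25 patients will be randomized to the intervention arm, and 25 will be in the control arm" (Study Design). Visit order: Recruitment, Enrollment, and Procedure, and Table 1.

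**The plan's own figure.** 6 × 8 + 2 = 50 men and 6 × 4 + 1 = 25 per arm. The scheme matches the planned size exactly.

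**Upper bound: the observer knows the block sizes and every earlier allocation.** In a block of 8, the last j places are determined when they all belong to the same arm. The probability is 2 × C(8−j, 4) / C(8, 4), with C(8, 4) = 70:

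- j = 1: 2 × 35/70 = 1
- j = 2: 2 × 15/70 = 3/7 (43%)
- j = 3: 2 × 5/70 = 1/7 (14%)
- j = 4: 2 × 1/70 = 1/35 (3%)

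The expected number certain per block of 8 is 1 + 3/7 + 1/7 + 1/35 = 56/35 = 1.6. In the block of 2 the second place always follows from the first, which adds 1. The total is 6 × 1.6 + 1 = 10.6 of 50 (21%). At least one place per block is always certain, so the total is never below 7.

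**Allowing for delay.** If the most recent allocation is not yet known, a place is certain only when it and the unseen one before it both lie in a run that must be a single arm. The j = 1 term drops out: 3/7 + 1/7 + 1/35 = 0.6 per block of 8, and 0 in the block of 2. The total is 6 × 0.6 = 3.6 of 50 (7%). With two unknown, 1/7 + 1/35 = 0.17 per block, or about 1 of 50 (2%).

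**Guessing.** For the fully informed observer, always guessing the arm with more places left is right, in a block of 2b, b + 2^(2b−1)/C(2b, b) − 1/2 times on average. That is 4 + 128/70 − 0.5 = 5.33 per block of 8, and 1 + 2/2 − 0.5 = 1.5 in the block of 2. The total is 6 × 5.33 + 1.5 = 33.5 of 50 (67%), against 50% by chance.

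**Varied blocks, as an illustration.** Assume sizes drawn at random from 4, 6 and 8, and an observer who knows that set and all past allocations but not the block boundaries. A simulation of 1,000 lists of 50 with the best possible guess gives about 1.1 certain allocations, and about 33.8 of 50 (68%) guessed correctly.

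**Timing.** "Study recruitment began on October 25, 2021, and the estimated study completion date is December 2024". Take completion as 31 December 2024. Going back 1 year, then 5 days, then 12 weeks gives 3 October 2023. Going back a further 8 to 28 days for treatment settings puts the last randomisation at about 5 to 25 September 2023. The article is dated 18 September 2023.

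**The case against.** The strongest objection is that the article does not place an observer with the necessary knowledge in the recruitment path. The interviewer is simply a physiotherapist. If that person does not treat the intervention arm, the statement on who is unblinded makes him or her blinded. A condensed article may also leave role separation and concealment to the full protocol. This stands, and it makes the point conditional.

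Timing weakens the point further. The interview is at the first visit, randomisation at the second and education at the third, so recent assignments may be unknown when a man is interviewed, and his own place in the sequence is not yet fixed. Over roughly 23 months, 50 men is about 2.2 a month, so a lag of 8 to 28 days covers about 0 to 2 men. The 21% is therefore a ceiling.

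A reader might infer several stronger things that the documents do not support:

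- That the physiotherapists learn every allocation. Teaching the intervention arm reveals intervention assignments; control assignments and the running order have to be reconstructed.
- That printing the scheme exposed the list. On the article's own dates it appeared at about the end of enrolment, so the possible route is knowledge within the team during recruitment.
- That the block of 2 is the last. That is the natural reading, but no order is given.
- That any resulting bias is beyond analysis. Baseline measures precede randomisation, so imbalance in measured factors can be seen and adjusted for. Only unmeasured factors, such as motivation, cannot.

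It is also fair to say that varying the block sizes does not reduce better-than-chance guessing. What survives is that the stated rule makes certain prediction possible for an informed recruiter, and that the one safeguard described does not address this.

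**Conclusion.** The concern holds in conditional form. The article contains no wrong figure or contradiction here; the weakness is in a stated design choice. Constant blocks of 8 and one of 2, in a single unstratified stream with unblinded treating staff, allow at most 10.6 of 50 allocations (21%) to be deduced on average, and 3.6 of 50 (7%) if the latest is not yet known.

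These figures assume sequential enrolment and an interviewer who knows the block sizes and the earlier allocations. The article leaves that open. It would be too strong to say that upcoming allocations in general are predictable: even for that observer most can only be guessed, with a 67% average success rate that includes the certain ones. It would also be too strong to say that selection bias has occurred.

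**What to change.** For any men still to be randomised:

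- Have the list holder generate randomly varied block sizes (for example 4, 6 and 8), withhold them from recruiting and treating staff, and use no block of 2. Start the new list at the end of a completed block.
- Where existing rostering allows, have the pre-consent interview done by a physiotherapist who does not deliver tele-RHB. This matters at least as much, because varied sizes remove nearly all certain predictions but leave guessing at about 68%.

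If enrolment is complete, report who knew the block sizes during recruitment and whether interviewers were separate from treating physiotherapists.

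The cost is a new list and a possible small departure from 25:25. Stopping inside a block of 8 leaves the arms at most 4 apart, that is 27:23. Then 1/27 + 1/23 = 0.0805, against 2/25 = 0.0800. With the planned difference of 8 and SD of 10, read as a two-sided two-group comparison, normal-approximation power goes from Φ(0.8/√0.0800 − 1.96) = 80.7% to Φ(0.8/√0.0805 − 1.96) = 80.5%.

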### Measures

#### Measurements and Examinations

All participants will take part in baseline, postintervention, and follow-up examinations. PSG will be performed by trained medical staff in accordance with recent guidelines [23]. The variables extracted from PSG will be AHI, oxygen desaturation index, supine AHI, total sleep time, average heart rate, mean oxygen saturation (SpO_2_), and the percentage of time with SpO_2_ saturation below 90%. PSG will be performed with Grael 4K PSG:EEG (Compumedics Limited). All of the above-mentioned data will be collected without the CPAP device in use.

Standardized questionnaires, including the 36-item Short Form Health Survey (SF-36), the World Health Organization’s tool to assess QoL (WHOQOL-BREF) [24], and ESS, will be filled in by all participants under the supervision of a medical specialist. The ESS questionnaire will be a tool for the participant’s subjective daytime sleepiness, and the SF-36 and WHOQOL-BREF questionnaires will assess the subjective perception of QoL.

Participants will undergo a bioelectrical impedance examination with InBody 370S (BridgePower Corp) to evaluate changes in body composition performed by trained medical personnel. Data on the participant’s sex, age, height, weight, and BMI will also be recorded. The monitored parameter will be the value of the percentage of body fat.

Participants will undergo a standardized 6MWT in accordance with American Thoracic Society guidelines to objectively assess their functional capacity by trained medical personnel [25]. The monitored parameter will be the distance in meters, which the participants will be able to walk in 6 minutes.

MIP and MEP will be measured with MicroRPM Respiratory Pressure Meter (Micro Direct Inc) and will be performed by a medical specialist based on recent recommendations for testing respiratory muscles [26,27].

Anthropometric parameters of the neck, waist, and hip circumference will be measured with a tape measure by trained medical staff. The current BMI value will also be calculated from actual body height and weight.

All participants undergo a standardized spirometric examination performed by a medical specialist with Spirobank II Basic (Medical International Research) in accordance with recommended procedures to objectively evaluate their lung function [28]. The parameters of forced vital capacity and forced expiratory volume in 1 second will be monitored.

All participants’ CPAP devices will be regularly remotely monitored by a Sleep Centre medical doctor to track CPAP compliance and adherence to treatment during their sleep-at-home conditions. Participants will use one of the following devices: AirSense 10 AutoSet (ResMed Inc) or Prisma 20A Auto CPAP (Löwenstein Medical Technology GmbH + Co. KG).

Participants will have laboratory blood tests with the intention of finding out the current values of their lipid profile. Values of the total cholesterol, triacylglycerols, high-density lipoprotein (HDL) cholesterol, low-density lipoproteins (LDL) cholesterol, and non-HDL cholesterol will be detected.

#### Primary Outcomes

Primary outcomes include changes from baseline in AHI, obtained from PSG; ESS score; SF-36 score; percentage of body fat; 6MWT distance; as well as MIP and MEP values.

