### Data Analysis

#### Statistical Analysis

TIBCO Statistica (TIBCO Software Inc) will be used for statistical analysis of the obtained data. Statistical analysis will be performed by a person blinded to the experimental conditions. The Shapiro-Wilk test will be used to assess the normality of the data obtained. To compare participants’ baseline and postintervention obtained data within the same group, a paired 2-tailed *t* test will be used for statistical analysis. When comparing the baseline and postintervention data of the participants between both groups, an unpaired *t* test will be used. The level of statistical significance will be set as *P*<.05. The acquired data will be securely collected on an encrypted external hard drive.

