#### Sample Size

A power analysis was performed based on a previous study by Hupin et al [37], and the expected improvement in AHI was estimated to be approximately 8 (SD 10) episodes per hour at the end of the program versus the baseline. The number of participants in each of the two groups (n=25), necessary to achieve such an effect size, was calculated by statistical analysis at 80% statistical power with α=.05.

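### Seven unranked primary outcomes share one unadjusted .05 level at 12 weeks, while the sample size gives the whole .05 to AHI alone

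*Protocol article*

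**What the plan says.** - **Outcomes.** The Primary Outcomes section reads: "Primary outcomes include changes from baseline in AHI, obtained from PSG; ESS score; SF-36 score; percentage of body fat; 6MWT distance". Two mouth pressures, MIP and MEP, complete the list. The Methods part of the Abstract gives the same seven: AHI, ESS, SF-36, percentage of body fat, 6MWT distance, MIP and MEP. Neither place ranks them.
- **Level.** Under Statistical Analysis: "The level of statistical significance will be set as *P*<.05". No division of the level, order of testing or adjustment accompanies it.
- **Tests.** The same section covers the comparison between arms by *t* test: "When comparing the baseline and postintervention data of the participants between both groups, an unpaired". It also covers change within an arm by *t* test: "To compare participants’ baseline and postintervention obtained data within the same group, a paired 2-tailed". Both concern baseline and postintervention data.
- **Sample size.** Under Sample Size: "the expected improvement in AHI was estimated to be approximately 8 (SD 10) episodes per hour". This is set at the end of the programme and leads to 25 per group at 80% power with α=.05. No other outcome has an assumed effect.
- **Success rule.** The Objective section hypothesises benefit across several domains. It does not say whether one, some or all of the primary outcomes must be significant for the programme to be called effective.

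**The concern.** A .05 level per test bounds the error of the main conclusion only if that conclusion rests on one test, or if a rule ties the tests together. Here seven outcomes have equal standing and no such rule is given. A report could call the programme effective on whichever primary outcome reached significance, even with no change in AHI, and still be consistent with the text.

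The sample size creates a second tension. It uses the whole .05 on AHI. If an adjustment across all seven were added later, the power stated for AHI would no longer hold. The primary outcome list, the level and the sample size therefore do not fit together as written, and an analysis plan could not settle this without changing one of them.

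**Working it through.** **Inputs.** Seven primary outcomes (Primary Outcomes); .05 for each test (Statistical Analysis); AHI difference 8, SD 10, 25 per group, 80% power, α=.05 (Sample Size). Assumptions of this check: the unpaired *t* test is two-sided (the article does not say), and the seven test statistics share one common correlation ρ, for which the article gives no value. Only the seven between-group tests at the postintervention visit are counted.

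**Step 1: the plan's own figure.**

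n per group = 2 × (1.960 + 0.842)² × (10/8)² = 2 × 7.85 × 1.5625 ≈ 24.5, rounded up to 25.

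This reproduces the stated 25. Power at n=25 is 80.7% by the normal approximation and 79.1% by the noncentral *t*. The match requires reading 8 (SD 10) as a difference between arms, although the article words it as a change from baseline. It confirms that the full .05 was used on AHI.

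**Step 2: at least one false significant result among seven, independent outcomes.**

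- Either direction: 1 − 0.95⁷ = 1 − 0.698 = 30.2%.
- Favouring tele-RHB only (.025 each): 1 − 0.975⁷ = 1 − 0.838 = 16.2%.

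**Step 3: correlated outcomes.** Seven standard normal statistics, Z_j = √ρ·U + √(1−ρ)·E_j, were simulated 300,000 times. The table gives the share of draws with at least one |Z_j| > 1.96, and with at least one Z_j > 1.96 in the favourable direction.

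| Assumed ρ | Either direction | Favouring tele-RHB |
|---|---|---|
| 0 | 30.2% | 16.2% |
| 0.3 | 27.2% | 13.7% |
| 0.5 | 23.0% | 11.5% |
| 0.7 | 17.9% | 8.9% |
| 0.8 | 14.8% | 7.4% |

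(The ρ=0 row is the exact value from step 2.) For a single test the nominal figures are 5% and 2.5%. From ρ=0.7 to ρ=0 the inflation is 17.9/5 = 3.6-fold to 30.2/5 = 6.0-fold in either direction, and 8.9/2.5 = 3.6-fold to 16.2/2.5 = 6.5-fold in the favourable direction.

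**Step 4: AHI power if the level is shared.** The first Holm step, like Bonferroni, tests at .05/7 = .0071. With 25 per group and a standardised difference of 8/10 = 0.8, AHI power at that level is 51% (noncentral *t*) or 56% (normal). To reach 80% at that level needs 41 per group (*t*) or 39 (normal). Holm loosens the threshold for AHI only if other outcomes are rejected first.

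**The case against.** The best defence is that the article is condensed and a multiplicity procedure often sits in the analysis plan, which is not shown. The hypothesis also joins its domains with a conjunction. If all seven had to succeed there would be no inflation, and if each domain were claimed separately each claim would keep its own 5% error. Part of this stands: the any-one-is-enough rule is one reading of a silent text, so the error rates are conditional on it. The defence does not remove the point, because the article itself fixes seven equal primary outcomes, one level and a sample size that spends all of that level on AHI.

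Some stronger readings are tempting but not supported:

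- **Two visits, fourteen tests.** All measurements are repeated one year after the programme: "on the fifth visit, participants of both groups will undergo the same examinations and measurements as they did at the baseline". A reader might infer fourteen primary tests and an error near 51% (1 − 0.95¹⁴). But Statistical Analysis describes tests of baseline and postintervention data only, Table 1 separates postintervention from follow-up, and Sample Size refers to the end of the programme. No 1-year test is stated.
- **18–30% as the rate of false success for the programme.** That range counts errors in both directions. The hypothesis is superiority of tele-RHB plus CPAP, so the matching range is about 9–16%.
- **About 19% power if all seven must succeed (0.79⁷).** This needs a standardised effect of 0.8 on every outcome, and independence. The article gives an effect for AHI only.
- **Several tests from SF-36.** The article names an SF-36 score in the singular, so extra tests are conjecture.
- **Trained or self-reported outcomes.** That the programme trains the muscles behind MIP and MEP makes a real effect likely, which is not a false positive. Self-report in ESS and SF-36 is a question of bias. Neither is multiplicity.

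**Conclusion.** The concern holds in a limited form. At the end of the 12-week programme, seven unranked primary outcomes are each tested at an unadjusted .05, only AHI is powered, and no success rule is given. If any one significant result counts as success, the chance of a false two-sided finding with no true effect is about 30% under independence and about 18% at ρ=0.7. In the direction favouring tele-RHB it is about 16% and 9%, against 2.5%. The independence figures follow directly from the stated level and count. The lower figures rest on an assumed correlation and would be smaller still at a higher one. As written, the .05 level does not control the error of the trial's main conclusion, and an adjustment across all seven would undo the stated power.

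**What to change.** Name change in AHI from baseline to the postintervention visit (visit 4) as the single primary outcome, at two-sided .05. It is the outcome that was powered, so 25 per group stays consistent with the Sample Size section. Make ESS, SF-36, percentage of body fat, 6MWT distance, MIP and MEP key secondary outcomes, tested with Holm at .05 across the six only if AHI is significant. Label all 1-year results secondary. Document this as a change made before unblinded analysis, and update the registry.

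If all seven must stay primary, declare Holm across them and state that AHI power at the first step (.05/7) is about 51% with 25 per group, not 80%.

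Cost: no new data are needed, but this is a mid-trial change, since recruitment began in October 2021, and it needs a stated reason. Under the first route six outcomes lose primary status. Under the second all seven, including AHI, face a stricter threshold.
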